### 8.5.2. Assessment of causality

The investigator is obligated to assess the relationship between investigational product and the occurrence of each AE/SAE. The investigator will use clinical judgment to

determine the relationship. Alternative causes, such as natural history of the underlying diseases, concomitant therapy, other risk factors and the temporal relationship of the event to the investigational product will be considered and investigated. The investigator will also consult the Investigator Brochure and/or Product Information, for marketed products, in the determination of his/her assessment.

There may be situations when a SAE has occurred and the investigator has minimal information to include in the initial report to GSK Biologicals. However, it is very important that the investigator always makes an assessment of causality for every event prior to transmission of the SAE Report Form to GSK Biologicals. The investigator may change his/her opinion of causality in light of follow-up information, amending the SAE Report Form accordingly. The causality assessment is one of the criteria used when determining regulatory reporting requirements.

In case of concomitant administration of multiple vaccines, it may not be possible to determine the causal relationship of general AEs to the individual vaccines administered. The investigator should, therefore, assess whether the AE could be causally related to vaccination rather than to the individual vaccines.

All solicited local (injection site) reactions will be considered causally related to vaccination. Causality of all other AEs should be assessed by the investigator using the following question:

Is there a reasonable possibility that the AE may have been caused by the investigational product ?

- NO : The AE is not causally related to administration of the study vaccine(s). There are other, more likely causes and administration of the study vaccine(s) is not suspected to have contributed to the AE.
- YES : There is a reasonable possibility that the vaccine(s) contributed to the AE.

Non-serious and serious AEs will be evaluated as two distinct events. If an event meets the criteria to be determined “serious” (see Section 8.2 for definition of serious adverse event), it will be examined by the investigator to the extent to be able to determine ALL contributing factors applicable to each serious adverse event.

Other possible contributors include:

- Medical history
- Other medication
- Protocol required procedure
- Other procedure not required by the protocol
- Lack of efficacy of the vaccine(s), if applicable

- Erroneous administration
- Other cause (specify).

## **8.6. Follow-up of adverse events and serious adverse events and assessment of outcome**

After the initial AE/SAE report, the investigator is required to proactively follow each subject and provide further information to GSK Biologicals on the subject's condition.

All AEs and SAEs documented at a previous visit/contact and designated as not recovered/not resolved or recovering/resolving will be reviewed at subsequent visits/contacts.

Investigators will follow-up subjects:

- with SAEs or subjects withdrawn from the study as a result of an AE, until the event has resolved, subsided, stabilized, disappeared, the event is otherwise explained, or the subject is lost to follow-up;
- or, in the case of other non-serious AEs, until they complete the study or they are lost to follow-up.

All Grade 3, Grade 4 or clinically significant laboratory abnormalities will be followed up until they have returned to normal, or a satisfactory explanation has been provided. Additional information (including but not limited to laboratory results) relative to the subsequent course of such an abnormality noted for any subject must be made available to the Study Monitor.

GSK Biologicals may request that the investigator perform or arrange for the conduct of supplemental measurements and/or evaluations to elucidate as fully as possible the nature and/or causality of the AE or SAE. The investigator is obliged to assist. If a subject dies during participation in the study or during a recognized follow-up period, GSK Biologicals will be provided with a copy of any available post-mortem findings, including histopathology.

New or updated information will be recorded on the originally completed SAE Report Form, with all changes signed and dated by the investigator. The updated SAE report form should be resent to GSK Biologicals within 24 hours of receipt of the follow-up information as outlined in Section 8.7.1.

Outcome of any non-serious AE occurring within 30 days post-vaccination (i.e. unsolicited AE) or any SAE reported during the entire study will be assessed as:

- Recovered/resolved
- Not recovered/not resolved
- Recovering/resolving
- Recovered with sequelae/resolved with sequelae

- Fatal (SAEs only).

## **8.7. Prompt reporting of serious adverse events to GSK Biologicals**

### **8.7.1. Time frames for submitting serious adverse event reports to GSK Biologicals**

SAEs will be reported promptly to GSK once the investigator determines that the event meets the protocol definition of an SAE. The investigator or designate will fax the SAE reports to GSK Biologicals' Study Contact for Serious Adverse Event Reporting **WITHIN 24 HOURS OF HIS BECOMING AWARE OF THESE EVENTS**. Additional or follow-up information relating to the initial SAE report is also to be reported to the GSK Biologicals' Study Contact for Serious Adverse Event Reporting within 24 hours of receipt of such information.

### **8.7.2. Completion and transmission of serious adverse event reports to GSK Biologicals**

Once an investigator becomes aware that a SAE has occurred in a study subject, she/he will report the information to GSK within 24 hours as outlined in Section 8.7.1. The SAE Report Form will always be completed as thoroughly as possible with all available details of the event, signed by the investigator (or designee), and forwarded to GSK within the designated time frames. If the investigator does not have all information regarding an SAE, he/she will not wait to receive additional information before notifying GSK of the event and completing the form. The form will be updated when additional information is received and forwarded to GSK **WITHIN 24 HOURS** as outlined in Section 8.7.1.

The investigator will always provide an assessment of causality at the time of the initial report as described in Section 8.5.2.

Facsimile (Fax) or electronic transmission of the SAE Report Form are the preferred methods to transmit this information to the Study Contact for Reporting SAEs. In rare circumstances and in the absence of facsimile equipment or electronic connection, notification by telephone is acceptable, with a copy of the SAE Report Form to follow. Initial notification via the telephone does not replace the need for the investigator to complete and sign the SAE Report Form within 24 hours as outlined in Section 8.7.1.

In the event of a death determined by the investigator to be related to vaccination, sending of the fax must be accompanied by telephone call to the Study Contact for Reporting SAEs.

**[contact]**

**Administrative Change, 16 February 2006**

## **8.8. Regulatory reporting requirements for serious adverse events**

The investigator will promptly report all SAEs to GSK in accordance with the procedures detailed in Section 8.7. GSK Biologicals has a legal responsibility to promptly notify, as appropriate, both the local regulatory authority and other regulatory agencies about the safety of a product under clinical investigation. Prompt notification of SAEs by the investigator to the Study Contact for Reporting SAEs is essential so that legal obligations and ethical responsibilities towards the safety of other subjects are met.

The investigator, or responsible person according to local requirements, will comply with the applicable local regulatory requirements related to the reporting of SAEs to the IRB/IEC and, if required, to the applicable government authority.

Investigator safety reports are prepared according to the current GSK policy and are forwarded to investigators as necessary. An investigator safety report is prepared for a SAE(s) that is both attributable to investigational product and unexpected. The purpose of the report is to fulfil specific regulatory and Good Clinical Practice (GCP) requirements, regarding the product under investigation.

An investigator who receives an investigator safety report describing a SAE(s) or other specific safety information (e.g., summary or listing of SAEs) from GSK Biologicals will file it with the Investigator Brochure or other appropriate study documentation and will notify the IRB or IEC, if appropriate according to local requirements.

## **8.9. Post-study adverse events and serious adverse events**

A post-study AE/SAE is defined as any event that occurs outside of the AE/SAE detection period defined in Section 8.4. Investigators are not obligated to actively seek AEs or SAEs in former study participants.

However, if the investigator learns of any SAE, including a death, at any time after a subject has been discharged from the study, and he/she considers the event reasonably related to the investigational product, the investigator will promptly notify the Study Contact for Reporting SAEs.

## **8.10. Pregnancy**

Not Applicable

## **8.11. Treatment of adverse events**

Treatment of any adverse event is at the sole discretion of the investigator and according to current good medical practice. Any medication administered for the treatment of an AE should be recorded in the subject's CRF. Refer to Section 6.9.

# **9. SUBJECT COMPLETION AND WITHDRAWAL**

## **9.1. Subject completion**

A subject who returns for the concluding visit/is available for the concluding contact foreseen in the protocol is considered to have completed the study.

A subject that comes for Clinic Visit 6 has completed the double-blind phase of the study. A subject that comes for Clinic Visit 7 has completed the single-blind phase of the study.

## **9.2. Subject withdrawal**

Subjects who are withdrawn for AEs must be clearly distinguished from subjects who are withdrawn for other reasons. Investigators will follow subjects who are withdrawn as

result of a SAE/AE until resolution of the event (see Section 8.6). Withdrawals will not be replaced.

### **9.2.1. Subject withdrawal from the study**

From an analysis perspective, a ‘withdrawal’ from the study is any subject who was not available for the concluding contact foreseen in the protocol.

A subject qualifies as a ‘withdrawal’ from the study when no study procedure has occurred, no follow-up has been performed and no further information has been collected for this subject from the date of withdrawal/last contact.

Investigators will make an attempt to contact those subjects who do not return for scheduled visits or follow-up.

Information relative to the withdrawal will be documented on the Study Conclusion page of the CRF. The investigator will document whether the decision to withdraw from the study was made by the subject’s parent or guardian or the investigator and which of the following possible reasons was responsible for withdrawal:

- serious adverse event
- non-serious adverse event
- protocol violation (specify)
- consent withdrawal, not due to an adverse event
- moved from the study area
- lost to follow-up
- death
- other (specify).

### **9.2.2. Subject withdrawal from investigational product**

A ‘withdrawal’ from the investigational product is any subject who does not receive the complete treatment, i.e. when no further planned dose is administered from the date of withdrawal. A subject withdrawn from the investigational product may not necessarily be withdrawn from the study as further study procedures or follow-up may be performed (safety or immunogenicity) if planned in the study protocol.

Information relative to premature discontinuation of the investigational product will be documented on the Vaccine Administration page of the CRF. The investigator will document whether the decision to discontinue further vaccination/treatment was made by the subject’s parent or guardian or the investigator and which of the following possible reasons was responsible for withdrawal:

- serious adverse event;
- non-serious adverse event;

- other (specify).

## **10. DATA EVALUATION: CRITERIA FOR EVALUATION OF OBJECTIVES**

### **10.1. Coprimary endpoints**

#### **10.1.1. Safety**

- Occurrence of SAEs from the time of first vaccination (Study Month 0) until one month post Dose 3 (Study Month 3).

#### **10.1.2. Immunogenicity**

- Anti-CS antibody titers one month post Dose 3.

### **10.2. Secondary endpoints**

#### **10.2.1. Safety and reactogenicity**

- Occurrence of solicited general and local reactions over a 7-day follow-up period (day of vaccination and 6 subsequent days) after each vaccination.
- Occurrence of unsolicited symptoms after each vaccination over a 30-day follow-up period (day of vaccination and 29 subsequent days).

#### **10.2.2. Immunogenicity**

- Anti-CS antibody titers prior to vaccination, one month post Dose 2 and one month post Dose 3.
- Anti-HBs antibody titers prior to vaccination, one month post Dose 2 and one month post Dose 3.

### **10.3. Tertiary endpoints**

#### **10.3.1. Immunogenicity**

*At Study Month 14:*

- Anti-HBs antibody titers determined 12 months post Dose 3.
- Anti-CS antibody titers determined at 12 months post Dose 3.

#### **10.3.2. Safety**

- Occurrence of SAEs from 1 month post Dose 3 until 12 months post Dose 3.

**10.4. Exploratory endpoints**

- Frequency of CS-specific T-cells prior to vaccination, one month post Dose 2, one month post Dose 3 and 12 months post Dose 3.
- Frequency of CS-specific B-cell memory prior to vaccination, one month post Dose 2, one month post Dose 3 and 12 months post Dose 3.
- Anti-CS antibody titers determined at 12 months post Dose 3 according to documented HBV immunization status at screening

**10.5. Estimated sample size**

A sample size of 75 evaluable subjects per group will have 90% power to demonstrate non-inferiority of RTS,S/AS02D versus RTS,S/AS01E in terms of anti-CS immune response (upper limit of 95% CI of the GMC ratio RTS,S/AS02D versus RTS,S/AS01E below 3.0) assuming a log Standard Deviation of 0.9 in both groups, alpha=0.025 (Pass 2000). It will be considered that non-inferiority is reached when the upper limit of the 95% CI of the anti-CS GMC ratio of RTS,S/AS02D to RTS,S/AS01E is below 3.0.

**10.5.1. Sample size for the primary safety endpoint**

Safety analyses will be performed on the Total Cohort. A trial of this size has the power to detect only large differences in the frequencies of AEs with reasonable power. A sample size of 75 evaluable subjects per group has the power to detect differences in the rates of safety endpoints between groups as shown in Table 11. Comparisons between groups will be done using Fisher's Exact test for each AE coded by preferred term (alpha = 0.05, 2 sided).

**Table 11 Differences in safety endpoints (between treatment groups that can be detected with 90% power for varying baseline rates)**

| Frequency of events for RTS,S/AS02D | Frequency of events for RTS,S/AS01E | Power to detect difference (number per group equals 75) |
|-------------------------------------|-------------------------------------|---------------------------------------------------------|
| 1%                                  | 13%                                 | 90%                                                     |
| 3%                                  | 18%                                 | 90%                                                     |
| 5%                                  | 21%                                 | 90%                                                     |
| 10%                                 | 29%                                 | 90%                                                     |

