## 3. STUDY DESIGN OVERVIEW

[figure not shown]

KEY: BS; Blood Sample. Vacc; Vaccination

- Experimental design: Phase II, single center, double-blind (observer blind, participant blind), randomized (1:1 ratio) trial with two groups in one study site.
- Healthy male and female children aged 18 months to 4 years of age will be screened; those determined to be eligible, based on the inclusion and exclusion criteria, will be enrolled in the study.

- Route of administration: all vaccines will be administered by the intramuscular route to the left deltoid.
- Each child will be observed for at least 60 minutes after vaccination to evaluate and treat any acute adverse events (AEs).
- This study will not capture cases of malaria for the analysis of efficacy. All cases of malaria presenting during the unsolicited period will be captured as unsolicited events. Cases at anytime during the study that meet the criteria for a SAE will be reported as SAEs.
- The access of the study population to HIV voluntary counseling and testing and HIV antiretroviral therapy according to national recommendations will be ensured, in collaboration with the government services.
- An insecticide impregnated bednet will be offered to all parent(s)/guardian(s) who present their child for screening.
- Blood for safety monitoring of hematology, renal and hepatic function will be measured at screening, one week post Dose 1, one month post Dose 3 and 12 months post Dose 3.
- Anti-CS antibody titers will be determined at screening, one month post Dose 2, one month post Dose 3 and 12 months post Dose 3.
- Anti-HBs antibody titers will be determined at screening, one month post Dose 2, one month post Dose 3 and 12 months post Dose 3.
- CMI and B-cell memory immune responses will be determined at screening, one month post Dose 2, one month post Dose 3 and 12 months post Dose 3.
- Timing of final analysis: 1 month post Dose 3. An annex safety analysis will be performed at the end of the study, one year post Dose 3.
- Data collection: conventional Case Report Form (CRF).

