#### **4.5. Number of subjects**

Children will be recruited by non-coercive methods according to existing policies of the study site (see Appendix C).

The necessary number of children will be screened in order to enroll approximately 180 eligible subjects, 90 to each group. See Section 10.5 for a detailed description of the criteria used in the estimation of sample size.

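### Table 11 prints 90% power for 75 children per group, but the two-sided Fisher test named beside it gives 80–84%; 75 is also not the planned size of the safety cohort

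*Protocol*

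**What the plan says.** Protocol section 10.5.1 fixes every input of the safety power statement.

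- **Size:** "A sample size of 75 evaluable subjects per group has the power to detect differences in the rates of safety endpoints". The column header of Table 11 repeats it: "Power to detect difference (number per group equals 75".
- **Test:** "Comparisons between groups will be done using Fisher's Exact test for each AE coded by preferred term (alpha = 0.05, 2 sided".
- **Result:** Table 11, captioned "Differences in safety endpoints (between treatment groups that can be detected with 90% power for varying baseline rates", gives four pairs of event rates (AS02D v AS01E): 1% v 13%, 3% v 18%, 5% v 21% and 10% v 29%. It prints 90% power for each.
- **Analysis set:** the section opens with "Safety analyses will be performed on the Total Cohort". Section 10.6.1 defines the Total Vaccinated Cohort, for safety, as every child with at least one documented vaccination. Section 10.8.1.1 analyses the coprimary SAE endpoint on it.
- **Planned enrolment:** section 4.5 will screen "in order to enroll approximately 180 eligible subjects, 90 to each group", and section 3 describes a "randomized (1:1 ratio) trial with two groups in one study site".

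**The concern.** Test, level, sidedness, group size and both rates are all printed, so the 90% can be checked from the protocol alone. Four pairs of whole-number rates giving exactly the same power would already suggest an approximate method, and Fisher's exact test is conservative at low event rates. The group size is a second problem. The Glossary ties evaluability to the according-to-protocol analysis, yet safety is analysed on everyone vaccinated, so the table describes a cohort that the safety analysis does not use.

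Safety to one month after Dose 3 is a coprimary objective, and the Synopsis describes this as the first study of RTS,S/AS01E in children. Table 11 is the only place where the protocol puts numbers on what the safety comparison can detect. The DSMB, which reviews the protocol under section 5.1.3.1, should be able to rely on it.

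**Working it through.** **Inputs** (section 10.5.1): n = 75 per group; two-sided α = 0.05; Fisher's exact test; rates p₁ (AS02D) and p₂ (AS01E) from Table 11. For the second calculation, n = 90 per group (section 4.5).

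**Method.** For every pair of counts (x, y), compute the two-sided Fisher p-value and mark the pair as a rejection if p ≤ 0.05. Then

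power = Σ Bin(x; n, p₁) × Bin(y; n, p₂), summed over all rejecting pairs.

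Defining the two-sided p-value by summing probabilities or by doubling the smaller tail gives the same power at both sizes.

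| AS02D v AS01E | Printed | Fisher, n = 75 | Fisher, n = 90 | AS01E rate for 90% at n = 75 |
|---|---|---|---|---|
| 1% v 13% | 90% | 79.9% | 89.3% | 15.3% |
| 3% v 18% | 90% | 83.6% | 91.2% | 19.9% |
| 5% v 21% | 90% | 80.6% | 88.4% | 23.8% |
| 10% v 29% | 90% | 80.0% | 87.8% | 32.2% |

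At n = 75 the shortfall runs from 90 − 83.6 = 6.4 to 90 − 79.9 = 10.1 points. At n = 90 it is at most 90 − 87.8 = 2.2 points, and the second row exceeds 90%. Reaching 90% at the printed rates would take about 92, 88, 96 and 96 per group.

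**Rounding.** Moving the AS01E rate by half a point either way keeps Fisher power at n = 75 between 76.9% and 85.6%. Rounding of that rate does not explain the gap.

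**Trying to reproduce the printed 90%.** The pooled normal approximation is

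power = Φ[(p₂ − p₁ − z·SE₀)/SE₁], with SE₀ = √(2p̄(1−p̄)/n), SE₁ = √(p₁(1−p₁)/n + p₂(1−p₂)/n) and p̄ = (p₁+p₂)/2.

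For 10% v 29% (difference 0.19):

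- n = 75, two-sided 5%: (0.19 − 1.96 × 0.0647)/0.0628 = 1.01, power 84.3%.
- n = 75, one-sided 5%: (0.19 − 1.645 × 0.0647)/0.0628 = 1.33, power 90.8%.
- n = 90, two-sided 5%: (0.19 − 1.96 × 0.0591)/0.0573 = 1.29, power 90.2%.

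All four rows, in table order:

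| Method | Power |
|---|---|
| Pooled z, two-sided, n = 75 | 82.8 / 85.7 / 83.7 / 84.3% |
| Enumerated Pearson chi-square, two-sided, n = 75 | 89.9 / 89.9 / 86.4 / 85.7% |
| Arcsine, two-sided, n = 75 | 90.8 / 89.9 / 86.6 / 85.6% |
| Pooled z, one-sided 5%, n = 75 | 89.8 / 91.8 / 90.4 / 90.8% |
| Pooled z, two-sided, n = 90 | 89.1 / 91.4 / 89.8 / 90.2% |

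Unpooled z, continuity-corrected z and Fisher mid-p were also tried. No two-sided 5% method tried at 75 per group gives 90% in all four rows. Only the last two lines of the table come close throughout, and each contradicts something printed: the first contradicts "alpha = 0.05, 2 sided", the second contradicts the 75 in the column header.

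**The case against.** The strongest objection is that the table is nearly right for the analysis that will be run. Safety uses all vaccinated children. Treatment numbers are assigned at Dose 1 (section 5.9), so children who drop out later stay in the cohort, and about 90 per group is the realistic size. There the Fisher test misses the listed differences about 9 to 12% of the time, against the 10% claimed. The AS01E rates giving 90% power at 90 per group are about 13.2%, 17.6%, 21.5% and 29.8%, each less than one point from the printed rate. Section 10.5.1 also warns that only large differences can be detected. The safety objective has no hypothesis, margin or success criterion, and results will be read with exact 95% confidence intervals. Enrolment rests on the anti-CS calculation in section 10.5, and dose progression on DSMB review. Neither uses Table 11.

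All of this stands, and it limits the severity. It does not make the table correct: 75, the two-sided Fisher test and 90% cannot all be true together.

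A reader might also infer that the sponsor used a one-sided test by mistake. The document does not support that. A two-sided calculation at 90 per group fits the four entries about as well, and 90 is a number in the protocol. A wrong sample-size label is at least as plausible as a wrong number of sides.

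**Conclusion.** The 90% in all four rows is wrong for the design as labelled. The two-sided 5% Fisher test at 75 per group has 79.9% to 83.6% power. The group size is also inconsistent with the stated safety cohort. Where the 90% came from cannot be settled from the protocol.

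It is tempting to conclude that the trial will miss these differences about twice as often as claimed (16–20% instead of 10%). That holds only for an analysis of 75 per group, which the protocol does not plan for safety. In the planned cohort, power is 87.8% to 91.2%, within about 2 points of the printed value. The correction is minor and leaves the design unaffected.

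The n = 90 figures assume that close to 180 children are enrolled 1:1 and receive Dose 1. All figures take the tabulated rates as exact and apply to a single comparison at the 5% level.

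**What to change.** Recompute Table 11 for the two-sided 5% Fisher exact test on the stated safety cohort. Three forms would be correct:

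- **Preferred:** set the group size to 90 (Total Vaccinated Cohort), keep the four rate pairs, and print about 89%, 91%, 88% and 88%.
- **Keep 75 and the printed rates:** print 80%, 84%, 81% and 80%.
- **Keep 75 and 90% power:** replace the AS01E rates with about 15%, 20%, 24% and 32%.

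The caption, the column header and the sentence introducing the table should then state the same size and power, and the section should use the cohort name defined in 10.6.1. The cost is one table and one or two sentences. The stated power becomes slightly less favourable in three rows of the preferred version. Enrolment, the test and the analysis sets stay as they are.
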